**Experiment 2**

**Training effects of musical training on Working Memory Performance.**
Research Questions:

(1)Does music training with a focus on pitch, timbre, and rhythm result in improvements in behavioral working memory performance in noise measures (greater percent of recall in SWIR working memory task)?(2)Does pitch and timbre-based training result in greater improvements in behavioral working memory performance in noise measures (greater percent of recall in SWIR working memory task) when compared to rhythm-based training?

**Experiment 3**

**EEG measures of musical training on Speech Understanding in Noise and Working Memory Performance.**
Research Question:

(1)Does music training alter EEG measures (alpha oscillation modulation) during the memory recall task of the SWIR?(2)Does music training alter speech neural tracking during the sentence understanding task of the SWIR?

## 3. Materials and Methods

This project is a collaboration of the Music and Health Research Collaboration (MaHRC) of the University of Toronto and the CI Program of Sunnybrook Health Center in Toronto, ON, Canada.

### 3.1. Participants and Sample Size

Participants will be recruited from Canada’s largest cochlear implant program at Sunnybrook Health Science Center in Toronto. Included will be postlingually deafened persons aged from 18 to 80 years, both uni- and bilateral implanted with at least 1 year of CI experience, and having native or bilingual fluency in English. Exclusion criteria will be single-sided deafness (SSD), severe cognitive deficits, and neurologic (e.g., stroke) or psychiatric disease. Participants will be asked to sign consent forms for participation, approved by the Research Ethics Board at Sunnybrook and the University of Toronto at their first meeting, and will be compensated for each session throughout the duration of the study.

Using the G-Power program [108], a sample size of 18 people for each of the three experimental groups was calculated (0.7 based on the upper and lower ranges of alpha event-related desynchronization in the digits in noise to obtain at least a 10% change from the baseline). We aim for 27 participants per group to account for subject attrition.

### 3.2. EEG Recording and Study Procedure

This project will apply a novel EEG approach that provides behavioral and electrophysiological measures of the SWIR test (SWIR-EEG). All EEG data will be recorded using a 64-channel actiCHamp Brain Products recording system (Brain Products GmbH, Inc., Munich, Germany). The EEG will be segmented by sentence length. The sentence envelope will be used as a reference calculation of the temporal response function (TRF) using the mTRF toolbox [101]. Dynamic imaging of coherent sources (DICS) [109] will be used to determine speech–brain coherence, and the source of alpha power (8–12 Hz) will be determined [64].

For EEG analysis, CI-related artifacts will be reduced using independent component analysis (ICA). The team of the Sunnybrook CI brain lab developed a technique to identify and remove CI artifacts using cross-correlation (or TRFs) with the stimulus envelope and the ICA activations [110]. Time–frequency analysis for preprocessed continuous data will be performed using either BESA (Brain Electrical Source Analysis) [111] or FieldTrip [112] in addition to applying custom scripts in Matlab and FieldTrip for more advanced analyses (e.g., TRFs with speech envelopes, across trial beamformer correlations).

The overall study procedure will comprise two pre-train sessions (4 h each) at Sunnybrook CI brain lab, eight music training sessions (50 min each) at MaHRC, and one post-train session (4 h) over a period of 3 months per participant. Prior to the first pre-train session, participants will complete online quality-of-life questionnaires (Speech Spatial Qualities (SSQ) [113], Cochlear implant quality of Life-10 (CI-QoL-10), Cochlear Implant Quality of Life-35 (CI-QoL-35) [114]). Behavioral measurements of clinical speech perception will be assessed through the Sentence Matrix speech test [115]. In addition, the AzBio Sentence Test [116] will be applied in a 3D listening setup in the first EEG session and be followed by the SWIR-EEG procedure (see Section 3.3). The SWIR-EEG procedure will be repeated in the second pre-train session 4 weeks later. Two pre-train sessions are required to account for the learning effects and stability of the EEG measures and to determine behavioral and EEG imaging differences in the post-session. After the third and post-EEG session, the participants will fill out a short online “musical background and CI-music training feedback questionnaire” designed by the first author (KM) (see Supplementary Materials).

The participants will be randomly assigned into three separate training groups by single-blinded permuted-block randomization ABC [117]. Groups A (pitch) and B (timbre) will be the experimental groups because these tasks involve mostly pitch cues and CI users typically have problems with this type of task. Group C (rhythm) will serve as a control, given that CI users typically perform well on rhythm tasks, and therefore the effects of training are expected to be minimal [2].

The music training (4 weeks in total) will start in the week after the second pre-train session. The participants will take part in eight one-to-one practice sessions led by certified Neurologic Music Therapists, scheduled twice per week with each session lasting 50 min. All three groups will follow a gradually challenging music training paradigm for each of the three conditions. The exercise protocol was developed by the first author based on principles of the effect of multi-modal musical training on auditory and speech processing and will involve both active instrument playing and focused listening to recorded music.

One post-train session will be scheduled one week after the music training to assess the short-term effects of the training by applying the online Sentence Matrix speech test [115] and the SWIR-EEG (see Figure 1 for the complete outline of the experimental paradigm).

### 3.3. The Procedure of the Sentence Final Word Identification and Recall Test (SWIR)

At first, the speech recognition threshold (SRT) for 85% correct sentence identification using HINT sentences will be determined by adaptively varying the signal-to-noise ratio of the sentence using speech-shaped noise. Each subject-specific SNR will be used in all of their repeated testing before and after music training. Participants will wear a 64-channel EEG cap and will be seated in a circular speaker ring array with a computer screen indicating instructions. The sentences will be presented by a speaker directly in front of the listener, while the other seven speakers will play speech babble. The test procedure will comprise twenty blocks of five HINT sentences in noise (SNR for 85% correct), where each block will include five trials of a list of six sentences. The participant will repeat the final word in each sentence (identification task). After each list, the participant will be asked to verbally repeat the last six words in any order (free recall task). The approximate time for this procedure will last about 50 min, including 10 min for the free recall task.

As mentioned before in Section 1.4 the SWIR test protocol enables the assessment of cognitive recall performance (WM) as indexed by the recall of the six final words of the sentence as well as subsequent speech understanding in noise.

### 3.4. Statistical Analysis

All data analysis including descriptive statistics will be performed using R [118]. Demographic data for each participant will include age, gender, etiology, handedness, years of education, and musical background. The grouping variable of interest will be “types of training” and will be coded into three categories: “A_pitch”, “B_timbre”, and “C_rhythm”. To test for differences after the training period within the three groups for each condition, one-way repeated measures ANOVA will be conducted. The 0.05 level of probability will be set as the level of statistical significance. The necessary assumptions for conducting a one-way repeated ANOVA should be met with the collected data. The participants in the three groups will be independent from each other, as they will be randomly assigned to the groups. The dependent variable “percentage of correctly identified words/sentence” is a ratio-measurement scale and will be tested to investigate if it is normally distributed before conducting the analysis. Levene’s test will be applied to test for homogeneity of variance among the groups. Should the one-way ANOVA analysis reveal that at least one group mean turns out as significantly different from the others; a post hoc test will be performed to detect which ones are significantly different from each other [119]. Differences between the groups will be analyzed with repeated measures ANOVA with three groups, an effect size of 80% power, and four repeated measurements. The 0.05 level of probability will be set as indicating statistical significance. Testing assumptions will be completed in the same format as the previous tests.

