In addition to training through analytical music listening, previous research has shown that playing/learning musical pieces integrates multiple sensory and motor systems. Playing an instrument creates an “action–perception link” between the motor and auditory systems of the brain [33,34]. While playing, auditory information must be constantly paired with motor activities (e.g., finger positions, lip tension) and sensory feedback. Continuous practice promotes auditory–motor plasticity and establishes strong connections between specific motor activities and precise corresponding acoustic information [35]. Furthermore, neuroscientific studies demonstrated an automatic coupling between auditory and motor systems when listening to rhythm and music (e.g., [36,37,38]). Enhanced activation in premotor areas was seen in both expert musicians and nonmusicians when they were listening to a melody they learned to play during short-term musical training [39]. Advanced rhythmic and musical skills seem to facilitate extracting temporal information of speech and thus improve understanding in the presence of background noise, as was shown in musicians [40].

Thus, auditory–motor (multi-modal) training may be more beneficial for CI users than purely auditory training [41]. Only sparse literature exists on the effects of multi-modal training on complex sound perception like vocal emotion recognition and pitch pattern recognition in CI rehabilitation. Chari et al. [42] tested the effect of a one-month computerized musical training on three groups of CI users (an auditory–motor group, an auditory-only group, and a no-training control group). Only the auditory–motor training group scored significantly better in the melodic contour identification task. These results support that short-term multi-modal music training significantly impacts pitch pattern recognition in CI users.

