**Experiment 1**

**Training effects of musical training on Speech Understanding in Noise**
Research Questions:

(1)Does music training with separate focuses on pitch, timbre, and rhythm result in improvements in behavioral speech in noise measures (greater percent correct in SWIR task)?(2)Does pitch- and timbre-based training result in greater improvements in behavioral speech in noise measures (greater percent correct in SWIR task) when compared to rhythm-based training?

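### The within-arm repeated measures ANOVA for question (1) does not carry through the learning control that the double baseline is meant to provide

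*Protocol article*

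**What the plan says.** Question (1) of Experiment 1 reads "Does music training with separate focuses on pitch, timbre, and rhythm result in improvements in behavioral speech in noise measures". Experiment 2 asks the same of working memory recall. The test named in Section 3.4 is: "To test for differences after the training period within the three groups for each condition, one-way repeated measures ANOVA will be conducted". The significance level is 0.05. A significant result is followed by a post hoc test, described as finding which group means differ.

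The schedule in Section 3.2 is "two pre-train sessions (4 h each) at Sunnybrook CI brain lab, eight music training sessions (50 min each) at MaHRC, and one post-train session". On the baselines it says "The SWIR-EEG procedure will be repeated in the second pre-train session 4 weeks later" and gives the reason: "Two pre-train sessions are required to account for the learning effects and stability of the EEG measures". The same sentence adds that they serve to determine the differences seen at the post session. Training follows: "The music training (4 weeks in total) will start in the week after the second pre-train session". The post session comes one week after training ends. Section 3.3 keeps each participant's signal-to-noise ratio the same at every test.

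On the comparator, Section 3.2 says "Group C (rhythm) will serve as a control, given that CI users typically perform well on rhythm tasks", and expects little effect of training in that arm. The between-group analysis in Section 3.4 assumes four repeated measurements.

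**The concern.** Section 3.2 expects participants to improve through repeating the test and adds a session to allow for it. Because the signal-to-noise ratio is fixed, any practice gain goes directly into the percentage score. All three arms are trained, so no between-arm comparison can separate training from practice for question (1). Only the untrained interval between the two baselines can help, and the named analysis does not say how that interval is used.

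At stake is the headline claim that music training improves speech in noise and working memory: it could be declared from test practice. A second risk concerns the rhythm arm. It is called a control, yet question (1) covers it as a training, and Section 1.2 says "Advanced rhythmic and musical skills seem to facilitate extracting temporal information of speech and thus improve understanding in the presence of background noise" (a finding that the article attributes to musicians). A null result for pitch and timbre against rhythm would therefore not show that training has no effect.

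**Working it through.** **Inputs from the protocol.** Three SWIR-EEG sessions (first baseline, second baseline, post); 18 per group calculated and 27 recruited; level 0.05. The first interval is 4 weeks. The second is the 4 weeks of training plus the week after it, plus up to a week before training starts: about 5 to 6 weeks.

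**Assumed, because the protocol gives no figure.** Learning L between the baselines of 0.2, 0.3 or 0.5 SD; correlation r between sessions of 0.5, 0.7 or 0.8, equal for all pairs.

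**The plan's own figure.** A paired two-sided test at 0.05 with a standardised effect of 0.7 and 80% power needs 19 participants; power at 18 is 79.9%. So 18 is reproduced within one participant, although Section 3.1 names neither the test nor the effect index. Then 18/(1 − 1/3) = 27 and 3 × 27 = 81. The point does not depend on this figure; it only sets the n used below.

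**Reading A: all three sessions are levels.** With no training effect and learning that stops at the second baseline, the session means are (0, L, L). Their squared deviations sum to (2/3)L², so the omnibus F has noncentrality n(2/3)L²/(1 − r). For n = 18, L = 0.3 and r = 0.7 this is 18 × 0.06/0.3 = 3.6, where a valid test of training would have 0.

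**Reading B: the baselines are averaged.** The expected gain is L − L/2 = L/2, so half the learning enters.

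**Reading C: second baseline and post only.** The expected gain is 0 if learning has stopped.

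Simulated rejection rates with no training effect (20,000 runs per case; the three figures are for r = 0.5, 0.7 and 0.8):

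| n | L (SD) | A: omnibus F | B: post − mean of baselines | C: post − second baseline |
|---|---|---|---|---|
| 18 | 0 | 5 / 5 / 5% | 5 / 5 / 5% | 5 / 5 / 5% |
| 18 | 0.2 | 12 / 17 / 24% | 8 / 9 / 11% | 5 / 5 / 5% |
| 18 | 0.3 | 22 / 35 / 50% | 11 / 15 / 20% | 5 / 5 / 5% |
| 18 | 0.5 | 54 / 78 / 92% | 21 / 33 / 44% | 5 / 5 / 5% |
| 27 | 0.2 | 17 / 25 / 36% | 9 / 11 / 15% | 5 / 5 / 5% |
| 27 | 0.3 | 33 / 50 / 70% | 14 / 20 / 28% | 5 / 5 / 5% |
| 27 | 0.5 | 75 / 93 / 99% | 30 / 47 / 63% | 5 / 5 / 5% |

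**Reading C when learning continues** (r = 0.7, n = 18). With means (0, L, 2L), it rejects in 18, 34 and 73% for L = 0.2, 0.3 and 0.5. With learning at half the rate, means (0, L, 1.5L), it rejects in 8, 12 and 26%.

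**Gain minus gain.** For (post − second baseline) − (second baseline − first baseline), a training effect T has expectation T under linear learning and T − L if learning has stopped. Its variance is 6(1 − r) against 2(1 − r) for a simple gain, a ratio of 3. At r = 0.7 and n = 18 with T = 0, it rejects in about 5% under linear learning. Under plateau it rejects in 9, 14 and 32%, and the drift is in the negative direction, so it does not create a false benefit.

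**The case against.** A reader might infer that the plan certainly counts learning between the baselines as training and leaves the second baseline unused. The documents do not support that. Section 3.4 does not list the levels of the factor, and its phrase about the period after training fits second baseline against post. Section 3.2 expressly gives the second baseline its role. A post hoc test inside one arm could only compare sessions, so post against second baseline may be among the comparisons; that comparison holds 5% if learning has stopped. The article is also a condensed account. The learning sizes and correlations are assumptions.

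These objections limit the claim but do not remove it. The article names a specific test, and under none of the three readings does that test compare the change over training with the change without training. The post hoc sentence speaks of groups, not sessions.

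A further fair objection concerns the remedy. Gain minus gain as the sole test would be a poor replacement: if L = T = 0.5 SD and learning has stopped, its expectation is zero and a real effect is missed. Per arm at n = 18, with 0.7 SD of the contrast detectable, it detects 0.7 × √3 = 1.2 SD at r = 0.5 and 0.7 × √1.8 = 0.94 SD at r = 0.7. Pooling would help, but the question is asked of each focus separately. This stands, so that contrast belongs beside the main one as a check.

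**Conclusion.** The concern holds in a limited form. Section 3.2 promises a control for learning, and the test in Section 3.4 does not deliver it. If all three sessions enter and the omnibus F is taken as the answer, false training effects arise in about 12 to 92% of arms at n = 18 and 17 to 99% at n = 27. These ranges rest on assumed learning of 0.2 to 0.5 SD that then stops, correlations of 0.5 to 0.8, and that reading of the plan. If only the second baseline and post are compared, the error is near 5% when learning has stopped and rises when it continues.

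Question (2) is less affected, because learning common to the randomised arms cancels in the group-by-time comparison. No contrast fully replaces an untrained arm, since the two intervals differ in length.

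**What to change.** Replace the omnibus test for question (1) as follows:

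- Fit one model over all three arms and all sessions, with post minus second baseline as the planned contrast. Give arm-specific and pooled estimates with intervals.
- Report second minus first baseline beside it. Pre-specify (post minus second baseline) minus (second minus first baseline) as a check for continuing learning. State its limits: three times the variance of a simple gain, downward bias if learning has stopped, and unequal intervals (4 weeks against about 5 to 6).
- Claim a training effect only if the gain over the training period is not explained by the change over the baseline period.
- State that a null pitch and timbre against rhythm result does not show absence of a training effect, because rhythm is also trained.
- State the session levels, and reconcile the four repeated measurements in Section 3.4 with the three SWIR-EEG sessions in Section 3.2.

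This needs no new visits or participants. The cost is a somewhat less favourable test of question (1), and a check with limited power within a single arm.

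### The pitch-and-timbre versus rhythm question is left to an omnibus three-group repeated measures ANOVA; one pre-specified contrast using both baselines would usually be more powerful at the same sample size

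*Protocol article*

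**What the plan says.** Section 2 asks, for speech in noise, "Does pitch- and timbre-based training result in greater improvements in behavioral speech in noise measures" than rhythm training does, and for working memory, "Does pitch and timbre-based training result in greater improvements in behavioral working memory performance in noise measures", again relative to rhythm. Section 3.2 makes pitch (A) and timbre (B) the experimental groups and rhythm (C) the control, in which little training effect is expected. It schedules two SWIR-EEG sessions before training and one after.

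Section 3.4 gives one between-group analysis: "Differences between the groups will be analyzed with repeated measures ANOVA with three groups", followed by "an effect size of 80% power, and four repeated measurements", at the 0.05 level with no sidedness stated. It does not say whether the group term or the group-by-session term is decisive. It names no contrast and no baseline covariate. The only follow-up, "a post hoc test will be performed to detect which ones are significantly different from each other", is described for the one-way ANOVA.

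On size, section 3.1 states "a sample size of 18 people for each of the three experimental groups was calculated", and then "We aim for 27 participants per group to account for subject attrition".

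**The concern.** The question is one comparison with 1 degree of freedom, and the planned test is an omnibus one. Group by session, with three sessions, has 4 df. It also looks for differences between A and B and for differences that arise between the two pre-training sessions. If the group main effect were used instead, an effect present only after training would be averaged with two sessions in which randomised groups have no true difference. In both cases some power is spent on departures that nobody asked about, and a real advantage of pitch and timbre training could be missed at a sample size that would be enough for a focused test.

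**Working it through.** **The plan's own figure.** The 18 per group can be reproduced, but not uniquely, because section 3.1 gives 0.7 without a metric and no correlation.
- Between-groups term of a repeated measures ANOVA, with f = 0.35 (0.7 read as d and halved), four measurements and r = 0.5 assumed: λ = 0.35² × 54 × 4 / (1 + 3 × 0.5) = 10.58. Power is 81% at 18 per group and 79% at 17, so n = 18.
- Paired t test with a standardised change of 0.7: power is 79.9% at 18, so n = 19.

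The origin of the 18 therefore does not show which test was intended. Nothing below depends on it.

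**Inputs.** From the article: three equal groups, n = 18 or 27 per group, two pre-training and one post-training SWIR session, alpha 0.05. Assumed: two-sided testing, SD 1 at each session, equal correlation r between sessions, A and B raised by d at the post session only, C unchanged. The article gives neither d nor r for SWIR. Its 0.7 comes from an EEG measure in another task.

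**Formulas.**
- Group main effect: λ = 2nd² / [9(1 + 2r)], with 2 and 3n − 3 df.
- Group by session: λ = 4nd² / [9(1 − r)], with 4 and 2(3n − 3) df.
- Adjusted contrast, (A+B)/2 − C at post: residual variance v = 1 − 2r²/(1 + r), noncentrality d / √(1.5v/n), with 3n − 5 df.

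**Worked case, n = 18, d = 0.7, r = 0.5.** Main effect: λ = 2 × 18 × 0.49 / 18 = 0.98, power 13%. Group by session: λ = 4 × 18 × 0.49 / 4.5 = 7.84, power 57%. Contrast: v = 0.667, noncentrality 0.7 / √(1.5 × 0.667 / 18) = 2.97, power 83%.

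| n per group | d | r | Group main effect | Group by session | Adjusted contrast |
|---|---|---|---|---|---|
| 18 | 0.5 | 0.5 | 9% | 31% | 55% |
| 18 | 0.5 | 0.7 | 8% | 50% | 74% |
| 18 | 0.7 | 0.5 | 13% | 57% | 83% |
| 18 | 0.7 | 0.7 | 11% | 82% | 95% |
| 27 | 0.5 | 0.5 | 11% | 46% | 73% |
| 27 | 0.5 | 0.7 | 10% | 70% | 90% |
| 27 | 0.7 | 0.5 | 17% | 78% | 95% |
| 27 | 0.7 | 0.7 | 15% | 95% | 99% |

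Simulation (3,000 runs per cell) agreed to within about 3 points, with type I error between 4.7% and 5.8% for every test.

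**Where the gain comes from.** Take the same contrast on post minus the mean of both baselines, with no covariates. Its variance is 1.5(1 − r): 0.75 at r = 0.5 and 0.45 at r = 0.7. Covariate adjustment lowers these to 0.667 and 0.424, a cut of 11% and 6%. In the worked case, power goes from 57% (group by session) to 78% (change contrast) to 83% (adjusted contrast). Most of the gain is thus the focused contrast using both baselines. Against post minus the second baseline alone, with variance 2(1 − r) = 1.00 or 0.60, the cut is 33% or 29%, but that comparator discards the first baseline.

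**If A and B differ.** With only one of them raised by d, the pooled contrast sees d/2, while λ for group by session is unchanged. At n = 18, d = 0.7, r = 0.5 the contrast has 31% power against 57%; at r = 0.7 it has 45% against 82%. If timbre has half the pitch effect (n = 27, d = 0.5, r = 0.5), the contrast has 49% and group by session 35%, and a 2-df baseline-adjusted test also has 49%.

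**Four measurements.** Section 3.4 says four, whereas section 3.2 schedules three SWIR-EEG sessions; the table uses three. With three pre-training and one post-training measurement (6 df for the interaction), n = 27, d = 0.5, r = 0.5 gives 8%, 44% and 76%, so the ordering is the same.

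**The case against.** The article is a condensed account, and a fuller analysis plan could name the decisive term, contrasts and covariates. A three-group repeated measures ANOVA is a valid test. This stands as far as validity goes: the point is one of efficiency. It does not remove the point, because section 3.4 positively names the between-group test, and a later plan would have to replace that wording.

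A reader might infer that the trial will test the group main effect and so has only 8–17% power, and might take the reproduction of 18 per group as confirmation. The documents do not support this. Question (2) asks about greater improvement, which is group by session, and the 18 fits a paired calculation almost as well.

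A reader might also infer that the contrast is always much more powerful. It is not. At 27 per group with d = 0.7 and r = 0.7 the gain is about 4 points, and the contrast loses outright if only one of the two trainings works. Section 3.2 treats A and B together as experimental groups but does not say that their effects are equal.

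**Conclusion.** The point holds as a mismatch between question and test, and the plan should be changed on it. The planned analysis is valid but, on the group-by-session reading, usually inefficient for question (2). In the cases tabulated, the adjusted contrast gains about 13 to 27 points of power, and about 4 points where group by session already reaches 95%. The loss would be far larger if the main effect were used, which the wording leaves possible. These sizes rest on assumed values of d and r, on equal correlation between sessions, and on pitch and timbre both working while rhythm does not. That last pattern follows the article's stated expectation for rhythm and its pooling of A and B, but equal effects in A and B are an assumption.

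**What to change.** In section 3.4, for each behavioural outcome (word identification and recall), state one pre-specified between-group analysis: the mean of A and B minus C on the post-train score, in a linear model with arm and both pre-train scores as covariates. The same contrast in a mixed model would also serve. Report A versus C and B versus C with confidence intervals beside it, and state that the pooled contrast has less power than the omnibus test if only one of the two trainings works. State whether the test is two-sided, and reconcile the four measurements with the three scheduled SWIR-EEG sessions.

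The cost is a change of wording. Both baselines are already collected, the comparison is already the stated question, and recruitment and procedures do not change.
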